## Abstract

**Background:**

The optimal management of chronic severe primary degenerative mitral regurgitation (MR) is to repair the valve but identification of the optimal timing of surgery remains challenging. Current guidelines suggest ‘watchful waiting’ until the onset of symptoms or left ventricular (LV) dysfunction but these have been challenged as promoting ‘rescue surgery’. Better predictors are required to inform decision-making in relation to the necessity and timing of surgery. Chronic volume overload is a stimulus for adverse adaptive LV remodelling. Subclinical reduction in LV strain before mitral repair predicts a fall in LV ejection fraction following surgery and is thought to reflect the development of myocardial fibrosis in response to chronic volume overload. Myocardial fibrosis can be detected non-invasively using cardiac magnetic resonance (CMR) imaging techniques as an expansion of the extracellular volume (ECV).

**Methods/design:**

This study investigates whether: 1) patients with above median ECV will have smaller reduction in end-systolic volume index (as a measure of the degree of reverse LV remodelling) on CMR following mitral valve repair, compared to those with below median ECV; and 2) higher ECV on CMR, validated through histology, adversely impacts upon post-operative complications and symptomatic improvement following surgery.

This is a multi-centre, prospective, cross-sectional comparison of patients prior to and 9 months following surgery for chronic severe primary degenerative MR. To establish the natural history of ECV in MR, an additional cohort of patients with asymptomatic MR who do not wish to consider early repair will be followed. Investigations include CMR, cardiopulmonary exercise test, stress echocardiography, signal-averaged electrocardiogram, 24-h electrocardiogram monitoring, laboratory tests and patient-reported outcome measures. Patients undergoing surgery will have cardiac biopsies performed at the time of mitral valve repair for histological quantification of fibrosis.

**Discussion:**

This study will advance our understanding of ventricular remodelling in MR, its impact on patient symptoms and ventricular response following surgery. Establishing the link between myocardial fibrosis (measured on CMR and validated through histology), with early ventricular dysfunction, will offer physicians a novel non-invasive biomarker that can further inform the timing of surgery.

**Trial registration:**

This trial was registered at ClinicalTrials.gov (NCT02355418) on 30th November 2015.

## Background

### Challenges in determining the optimal timing of surgery

Mitral regurgitation (MR) is the most common form of valvular disease in the USA, affecting 2.5% of the general population and over 10% of those aged 75 years and older [1]. It is the second most frequent valve disease requiring surgery in Europe, and the prevalence of moderate-to-severe MR is expected to double by 2030 due to an ageing population [2]. Improvements in the diagnosis, quantification and surgical techniques for repair of a primary degenerative mitral valve (MV) now allow restoration of normal life expectancy following surgery [3].

Current AHA/ACC/ESC guidelines recommend expectant management until class 1 indications for surgery are reached, namely development of NYHA II-IV symptoms; LV ejection fraction (LVEF) <60% or LV internal diameter in systole ≥40 mm [4, 5]. Unfortunately, in spite of clear guidelines on the timing of surgery, a fifth of patients with severe primary MR continue to present post-operatively with reduced ejection fraction and an increased risk of congestive cardiac failure [6] despite single surgeon [7] and single centre [8] studies suggesting that better outcomes may be achieved. Class IIa indications for (MV) repair in asymptomatic patients at low surgical risk are also widely followed, although there is evidence for this from only one randomised study [9]. Proponents for earlier surgery make reference to registry data showing that repair in asymptomatic MR may result in better LV function, lower rates of heart failure and stroke [10], and normal life expectancy [7].

Careful surveillance with surgery delayed until class 1 indications are met, however, may deliver outcomes that are equally as good as early MV repair. In a study of 132 consecutive patients, a programme of regular (3–12 monthly) review with referral based on Class 1 indications delivered survival rates equivalent to the general population, both in those proceeding with surgery and in those who were managed conservatively; 55 ± 6% avoided surgery altogether at 8 years without compromising their outcome [11]. Since primary MR increases in prevalence with age and given the ageing of the population in Europe, there are likely to be increasing numbers of patients who may wish to avoid surgery while they feel well, providing their long-term outcome is not compromised. Moreover, there is the potential for problems with an approach that pushes asymptomatic patients through major cardiothoracic surgery in the absence of randomised trial evidence. Firstly, by definition, surgery cannot improve quality of life if the individual is truly asymptomatic but does commit the patient to a period of rehabilitation and is associated with a minimum mortality risk of 1%. Secondly, the ability to identify a reparable MV is imperfect and not everyone who expects a repair receives one. In the UK, only 64.6% of patients undergo repair but in the study by Kang et al. which recruited only those with ‘reparable’ valves, 6% still ended up with replacement [9]. Operative mortality in those planned for repair but ultimately requiring replacement is high. Finally, although MV repair is usually successful and long-lasting, this is not always the case (reoperation rate of 11–28% at 15 years) with one third having a late recurrence of moderate or severe MR [12]. In the absence of large-scale randomised data, debate continues [13, 14].

### Ventricular remodelling to guide the timing of surgery

Whilst patients may possess the same degree of MR for a similar duration, their ventricular function and symptom status may be quite different, suggesting that differential ventricular remodelling may be a potential underlying factor that influences the onset of surgical indications. In contrast to the traditional concept that there is a transition point from ‘compensated’ to ‘decompensated’ chronic primary MR, there is strong evidence that left ventricular (LV) remodelling is progressive from the earliest stages of MR with a reduction in early myocardial velocity and global strain [15, 16]. This sub-clinical reduction in contractility is in turn reflected in LA dilatation due to elevated LV end-diastolic pressure [17] and progressive secondary right ventricular failure [18]. Sub-clinical LV dysfunction is measured through change in strain via a number of methodologies, including tissue Doppler, speckle tracking echocardiography and feature-tracking CMR (FT-CMR), and predicts both the onset of symptoms [16] and the degree of reverse LV remodelling following MV repair [19]. Sub-clinical changes in LV systolic deformation, impaired diastolic relaxation and elevated LA pressure are frequently ascribed to the presence of interstitial fibrosis [20], with autopsy studies confirming that this develops in patients with MR of varying degrees of severity [21].

Characterising change in myocardial contractility in MR by fall in ejection fraction, increase in linear dimension and volume, or change in strain, whether using echocardiography or CMR, is difficult because all these techniques are volume-dependent. The evolution of CMR T1 mapping techniques offers a completely different approach that is non-invasive, quantitative but is not dependent on chamber size or volume status, since the aim is to identify interstitial myocardial fibrosis as a marker of ‘myocardial stress’ in MR [22]. T1 mapping has been validated against histology as a method for measuring interstitial fibrosis mainly in aortic stenosis, inherited cardiomyopathies and all-cause heart failure [23–25] with increasing T1 and ECV associated with increased morbidity and mortality [26, 27]. Sequences allow construction of parametric pixel-wise colour T1 map to quantitatively measure the longitudinal myocardial relaxation time before and after gadolinium contrast administration for measurement of T1 times and calculation of myocardial ECV. Using this technique, a strong linear correlation has been demonstrated between ECV and histological collagen volume fraction measured in aortic stenosis and explanted hearts of patients undergoing heart transplantation [28]. In a pilot study of 24 patients (mean age 62 +/− 16 years) with primary degenerative moderate or severe asymptomatic MR with no class I indication for surgery, we previously found a significant increase in ECV compared to age and gender-matched controls [29]. The extent of fibrosis correlated both with exercise capacity and a reduction in longitudinal strain.

Therefore, this study aims to assess whether left ventricular fibrosis as measured through CMR impacts upon patient outcomes including ventricular recovery following surgery, post-operative complications and symptomatic improvement. The primary endpoint of this study is the reduction in end-systolic volume index on CMR (as a measure of reverse LV remodelling) at 9 months following surgery, comparing those with ECV measured pre-operatively above and below the median. The reduction in left ventricular end-systolic volume index (LVESVi) is a commonly measured outcome parameter for the quantification of reverse left ventricular remodelling in MR [9, 30]. Secondary end-points (Table 2) assess the difference in exercise performance, symptom status, post-operative recovery and ventricular contractility (measured by LVEF and myocardial strain) between patients with an above and below-median ECV before and 9 months after MV surgery.

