### Power calculation

Applying in-house pilot data and informed by previous CMR studies [42], we expect the standard deviation of LV end-systolic volume indexed to body surface area (ESVi) will be 12 ml/m^2^. A survival advantage has previously been shown with a 7 ml/m^2^ difference in ESVi from pre- to post-surgery in patients with asymptomatic MR [9]. This change has been selected as a clinically-significant difference for the study; hence it is powered on a comparison of the change in ESVi between two groups: those above and below median ECV. An independent samples t-test with 48 patients per group (96 total) and a within-group standard deviation of 12 ml/m^2^ yield a minimum detectable difference of 7 ml/m^2^ at 80% power, with alpha = 0.05. We therefore plan to recruit 115 subjects allowing for a 15% drop-out rate.

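### Splitting pre-operative ECV at the sample median is valid but inefficient; analysing ECV as a continuous variable would use the same data better

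*Protocol article*

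**What the plan says.** The median split appears in three linked places in the protocol article.

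- Abstract, Methods/design: the first hypothesis is that "patients with above median ECV will have smaller reduction in end-systolic volume index" after repair.
- Background, Ventricular remodelling to guide the timing of surgery: the primary endpoint is the fall in ESVi at 9 months, "comparing those with ECV measured pre-operatively above and below the median". The same paragraph applies the split to secondary comparisons of exercise performance, symptom status, post-operative recovery, ejection fraction and strain.
- Methods/design, Power calculation: "hence it is powered on a comparison of the change in ESVi between two groups: those above and below median ECV", using an independent samples t-test with 48 patients per half, "a within-group standard deviation of 12 ml/m^2", which is said to "yield a minimum detectable difference of 7 ml/m^2^ at 80% power, with alpha = 0.05".

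The article gives no numeric ECV cut-off and describes no analysis of ECV as a continuous variable. The Background section describes remodelling in MR as progressive from its earliest stages rather than as a switch between two states. It presents T1 mapping as a quantitative technique and reports a linear correlation of ECV with histological collagen in other conditions. The Abstract's Discussion says that establishing the link between fibrosis and early dysfunction "will offer physicians a novel non-invasive biomarker that can further inform the timing of surgery".

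**The concern.** ECV is measured on a continuous scale, but the primary test keeps only which half of the cohort a patient falls in. Two patients just either side of the median are treated as different, while a patient just above it is treated the same as the patient with the highest value. If the outcome changes gradually with ECV, as the Background suggests, that discards information in a study sized at 80% power.

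The second issue is interpretation. The cut is whatever the median of the recruited cohort turns out to be. Table 1 names no minimum severity of MR, and subgroup analyses by severity are planned, so case mix can move it. A result for the upper against the lower half of this cohort cannot be applied directly to a new patient with a measured ECV, which is the use that the protocol has in mind for the marker.

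**Working it through.** **Inputs from Power calculation:** difference 7 ml/m², within-group SD 12 ml/m², 48 per half (96 in all), alpha 0.05. Sidedness is not stated; two-sided is assumed because it reproduces the stated power (one-sided would give 88.7%).

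**Step 1: reproduce the plan's figure.**
- Standardised distance = 7 / (12 × √(2/48)) = 7 / 2.449 = 2.858.
- Normal approximation: Φ(2.858 − 1.960) = 81.5%.
- Noncentral t: 80.7%. Minimum detectable difference at 80% power: 6.93 ml/m².

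The stated 80% and 7 ml/m² are correct.

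**Step 2: translate the planned difference into a slope.** Assume normal ECV and a linear relation with change in ESVi.
- Gap between the mean ECV of the two halves = 2√(2/π) = 1.596 SD of ECV.
- Slope = 7 / 1.596 = 4.39 ml/m² per SD of ECV.
- Residual SD = √(144 − 4.39² × (1 − 2/π)) = √(144 − 6.99) = 11.71.
- Correlation r = 4.39 / √(4.39² + 11.71²) = 4.39 / 12.5 = 0.351.

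**Step 3: power of the continuous analysis at n = 96.**
- Fisher z: Φ(atanh(0.351) × √93 − 1.960) = Φ(3.53 − 1.96) = 94.2%.
- Simulation, 20,000 replicates: 94.4%.
- Noncentral F for the slope, noncentrality 96 × r²/(1 − r²) = 13.5: 95.3%.

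Under these assumptions the share of information lost by the split is about 1 − 2/π = 36%. About 59 patients analysed continuously match the power of 96 analysed by halves.

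**Step 4: vary the assumptions.** The gap of 7, the within-group SD of 12 and n = 96 are held fixed.

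| ECV distribution and relation | Continuous | Median split |
|---|---|---|
| Normal, linear | 94% | 80% |
| Uniform, linear | 90% | 79% |
| Bimodal, linear | 88% | 79% |
| Right-skewed, linear | 97–98% | 80–81% |
| Right-skewed, linear in log ECV | 92% | 80% |
| Normal, step exactly at the population median | 60–61% | 73–74% |

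In the last row the split itself falls below 80% because the sample median does not coincide exactly with the population median.

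**Step 5: would a spline check reveal the unfavourable case?** With a step at the median, a 3-knot spline test of non-linearity (knots at the 10th, 50th and 90th percentiles) rejected in 5.6% of simulated trials, essentially its 5% false-positive rate. It rejected in 63% when the step was at the upper quartile, a shape where the slope already had more power than the split.

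**The case against.** The strongest defence is that nothing here is wrong. Hypothesis, primary comparison and power calculation agree with one another, the t-test controls its error rate, and the study reaches its declared power with its declared analysis. All of that stands. A reader might infer that the study is underpowered or the sample size miscalculated; the reproduced 80.7% shows otherwise.

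Further points stand in part or in full:

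- **The gain is conditional.** The article gives neither a distribution for ECV nor a shape for its relation with change in ESVi. The linear correlation it reports is between ECV and collagen, not between ECV and remodelling. A flat claim of 95% power is therefore not supported; a range is.
- **A slope supplies no threshold either.** It would be wrong to fault the split for lacking a transferable cut-off and offer the slope as the cure. What the slope adds is an expected recovery at a measured ECV.
- **The aim is not defeated.** A comparison of halves can show whether ECV is associated with recovery, and the Discussion section speaks of further informing decisions and of a rationale for larger trials.
- **The scope is limited.** Table 2 also lists ECV itself as a secondary endpoint, and the histological validation is not described as a median split. Only the secondary comparisons named in the Background are affected.
- **The spline is not a full safeguard**, as Step 5 shows.

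A statistical analysis plan might add a continuous analysis. That does not remove the point, because this document fixes the split as primary and powers the study on it.

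**Conclusion.** The point holds as a recommended efficiency improvement. With the plan's own difference and SD, and assuming roughly normal ECV and a linear relation, a continuous analysis raises power from 80.7% to about 94–95% in the same 96 patients. The risk of missing the planned effect falls from about 19% to about 5–6%. Across the other linear or log-linear shapes tried, power is about 88–98%, against 79–81% for the split. Only a step exactly at the median reverses the ranking, and the article's account of progressive remodelling gives no reason to expect one. Separately, the split's result is tied to this cohort's median and cannot be applied directly to a new patient's ECV.

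**What to change.** - State the primary test as the slope of change in ESVi on continuous pre-operative ECV. Express it per fixed unit, such as 5 percentage points, rather than per sample SD, which would again depend on the cohort.
- Pre-specify a spline as a check on shape, described as a check and not as a guarantee.
- Keep the above/below-median comparison, with its 7 ml/m² power basis, as a supporting analysis.
- Use continuous ECV for the secondary outcomes that the Background compares by median.

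**Cost.** The change is to wording only: no extra patients, scans or biopsies, and 96 analysed patients remain sufficient under the linear and log-linear shapes tried. The primary hypothesis must be reworded, and this should be done before outcomes are examined. The article gives no clinically important slope. The 7 ml/m² gap corresponds to 4.39 ml/m² per SD of ECV under normality, so restating it per 5 points needs the SD of ECV (4.39 × 5/SD), which the sponsor would have to supply from its pilot data. The slope test assumes an approximately linear, or at least monotone, relation. It would lose power if the truth were a step at the median, a shape that the spline would not reliably detect.

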## Methods/design

### Study design

This is a multicentre prospective, cross-sectional comparison of patients with primary degenerative MR before and after MV repair. To establish the natural history of ECV in MR, an additional cohort of patients with asymptomatic MR who are not eligible or do not wish to consider early MV repair (via a class IIa surgical indication) will be followed. Study design is illustrated in Fig. 1; details of the inclusion and exclusion criteria and the study endpoints are detailed in Tables 1 and 2 respectively.

**Fig. 1 Fig1:**
[figure not shown]
Study design flowchart

**Table 1 Tab1:** Inclusion and exclusion criteria

Inclusion criteria
Age 18 and over
Primary degenerative mitral regurgitation (diagnosed and quantified according to the European Association of Echocardiography guidelines)
Exclusion criteria
Secondary mitral regurgitation
Primary mitral regurgitation not due to degenerative disease (including rheumatic disease)
Co-existing moderate or severe aortic valve disease
Congenital heart disease
Inherited or acquired cardiomyopathy
Non-incidental or symptomatic coronary artery disease
Uncontrolled atrial fibrillation (resting heart rate > 100/min)
Pregnancy
Unable to undergo CMR
Unable to undergo cardiopulmonary exercise test

**Table 2 Tab2:** Primary and secondary study end points

Primary end point
Change in end-systolic volume index on CMR (as a measure of reverse LV remodelling)
Secondary end points
Exercise capacity assessed by peak VO_2_ using treadmill or bicycle
Health related quality of life assessed using the functional domain of SF-36
Extracellular volume on CMR
Ejection fraction and global myocardial strain on CMR
Measures of surgical outcome including inotrope and IABP usage, time to extubation, ITU and hospital length of stay, post-operative weight gain (pre-op to post-op day 4)

The surgical centres participating in the trial will be the University Hospital Birmingham NHS Foundation Trust, University Hospitals Coventry and Warwickshire NHS Trust, and The Royal Wolverhampton NHS Trust.

### Baseline studies

#### Cardiac magnetic resonance imaging

All patients will undergo 1.5 T multiparametric CMR at the University Hospital Birmingham site (1.5 Tesla scanner Magnetom Avanto, Siemens). Vertical long axis (VLA) and horizontal long axis (HLA) SSFP cine imaging (retrospective electrocardiographic gating, SSFP) of the left and right ventricles are performed. These images will be used to pilot the LV short axis stack acquired using serial contiguous short axis cines (typical parameters to be achieved: resolution 40–50 msec, repetition time 3.2 msec, echo time 1.7 msec, flip angle 60, field of view 300 mm, in-plane resolution 1.5 × 1.5 mm^2^, slice thickness 7 mm with 3 mm gap, minimum 25 phases per cardiac cycle) in accordance with previously validated methodology [31]. MV anatomy will be assessed using dedicated planes traversing the A1/P1 A2/P2 and A3/P3 scallops of the MV.

Analysis of ventricular function, volume and LV mass will be performed offline with delineation of papillary muscles and trabeculations using thresholding (cvi42® version 5.3.4, Circle Cardiovascular Imaging, Canada). Measurements will be made off-line using the contiguous short axis multi-slice acquisition with delineation of atria/ventricles confirmed in matched long axis planes [31]. For ventricular volume analysis, the endocardial border will be detected and the largest and smallest cavity volumes are defined as end-diastole and end-systole respectively. The endocardial border is defined as the boundary between blood pool and myocardium, with papillary muscles excluded from volumes. Mitral regurgitant volume (MRV) will be calculated as the difference between LV stroke volume (LVSV) and the aortic forward stroke volume (AoSV). Regurgitant fraction (RF) will be calculated as RF (%) = (MRV/LVSV) × 100.

Myocardial deformation will be assessed using 3D feature-tracking on CMR (FT-CMR) using cvi42® (version 5.3.4, Circle Cardiovascular Imaging, Canada). 3D FT-CMR will be performed using smoothed endocardial and epicardial borders in the end-diastolic frame of all short and long axis slices before defining the superior RV insertion points within the LV. Peak systolic strain, early diastolic strain rate and late diastolic strain rate will be recorded in the circumferential, radial and longitudinal directions.

For myocardial characterisation, myocardial and blood relaxation times pre- and 15 min after gadolinium contrast administration will be measured offline to calculate T1 times and ECV using cvi42® software as per European Society of Cardiology consensus statement [32]. All T1 maps will be checked for the presence of breathing, susceptibility and gating related artefacts. To avoid the blood-myocardial boundary, 20% offset both from the epicardial and endocardial borders will be employed and care taken to avoid any areas of LGE. Extracellular volume will be calculated using myocardial and blood T1 values before and after contrast using validated formulae [33], ECV = λ * (1 – haematocrit), where:$$ \uplambda =\frac{\frac{\mathsf{1}}{\mathit{\mathsf{T}}{\mathsf{1}}_{\mathit{\mathsf{myo}}\;\mathit{\mathsf{post}}}}-\frac{\mathsf{1}}{\mathit{\mathsf{T}}{\mathsf{1}}_{\mathit{\mathsf{myo}}\;\mathit{\mathsf{pre}}}}}{\frac{\mathsf{1}}{\mathit{\mathsf{T}}{\mathsf{1}}_{\mathit{\mathsf{blood}\mathsf{post}}}}-\frac{\mathsf{1}}{\mathit{\mathsf{T}}{\mathsf{1}}_{\mathit{\mathsf{blood}}\ \mathit{\mathsf{pre}}}}} $$

Haematocrit for ECV calculation is be measured contemporaneously with the CMR study.

